### 2.8. Blinding

Blinding of care providers is not possible, because those in the intervention group will receive teleconsultation support. The patients, outcome assessors, recruiters, data managers, and the data safety monitoring committee will be sought blinded. 

Two independent blinded statisticians will perform statistical analyses with the two intervention groups coded ‘A’ and ‘B’. The steering group will draw two blinded conclusions: one assuming ‘A’ is the experimental group and ‘B’ is the control group—and one assuming the opposite. Based on these two blinded conclusions, two abstracts will be written (and published as a supplement to the primary publication). When the blinding is broken, the ‘correct’ abstract will be chosen, and the conclusions in this abstract will not be revised.

### 2.9. Data Retention

Once a patient and the corresponding physician and practice are recruited, the research team will apply and monitor the retention rate. We will disseminate the project in social media to increase awareness, adhesion, and retention of the primary care physicians in the project. 

In the intervention group, the teleconsulting team will promptly respond to physicians’ requests, use communication tools that best suit their routine, and consider the practice and patient’s context to deliver a feasible teleconsultation. Those features were assessed during the feasibility test, with favourable results. These factors will increase participant and data retention. A dedicated researcher will monitor the teleconsulting process, ensuring that physicians evenly receive high-quality support. Discontinuation of participants’ adherence after enrolment will be used for censoring and analysed following an intention-to-treat principle.

### 2.10. Data Management

The research team has a secure REDCap© environment hosted at the National Institute of Cardiology of Brazil server, where databases and forms will be created and hosted, comprising data from primary care practices and physicians collected from public websites, randomisation lists, reports shared by the municipality about hospital admissions, primary care clinical data, mortality data, recruitment assignments and monitoring, and the answers to patient-reported outcomes questionnaires. A database and a reporting system have been developed within the e-consultation platform for management of intervention data, hosted at a secure web domain contracted by the project team. 

Researchers will only have access permission to data concerning their specific activities (e.g., recruiter, teleconsultant, data analyst) on REDCap© and the e-consultation platforms. Access will be granted through individual passwords changed regularly. The data manager will perform a weekly scheduled backup to a different server. 

For analysis, all data will be merged into one single database on the study’s REDCap© environment, based on the patients’ single identifier numbers (CPF). The data management team will monitor missing data and apply measures to communicate and minimise any lack. We will store the complete database for one year after the end of the study and share anonymised datasets in a dataset repository. 

### 2.11. Statistical Analysis

#### 2.11.1. Sample Size

We calculated the sample size based on the primary outcome, considering the expected values and differences between groups as described in an extensive European survey of heart failure morbidity, which reports a composite index of readmissions and mortality of 40.1% per year [19]. The estimated effect size based on similar interventions described in the literature is 30% [27]. Assuming an intra-cluster correlation (ICC) of 0.05 based on similar studies in primary care [28], a minimum of 72 clusters of 10 patients in each cluster are necessary to detect a 15% difference in the primary outcome with 95% significance (5% type I error) and 80% power (20% type II error). Based on this sample size, we have estimated the power of all remaining outcomes.

For calculations, we used the sample size calculator for cluster randomized trials by the Health Services Research Unit from Aberdeen University [29] and the R software package “CRTsize”.

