## Abstract

Heart failure is a prevalent condition and a frequent cause of hospital readmissions and poor quality of life. Teleconsultation support from cardiologists to primary care physicians managing patients with heart failure may improve care, but the effect on patient-relevant outcomes is unclear. We aim to evaluate whether collaboration through a novel teleconsultation platform in the Brazilian Heart Insufficiency with Telemedicine (BRAHIT) project, tested on a previous feasibility study, can improve patient-relevant outcomes. We will conduct a parallel-group, two-arm, cluster-randomised superiority trial with a 1:1 allocation ratio, with primary care practices from Rio de Janeiro as clusters. Physicians from the intervention group practices will receive teleconsultation support from a cardiologist to assist patients discharged from hospitals after admission for heart failure. In contrast, physicians from the control group practices will perform usual care. We will include 10 patients per each of the 80 enrolled practices (n = 800). The primary outcome will be a composite of mortality and hospital admissions after six months. Secondary outcomes will be adverse events, symptoms frequency, quality of life, and primary care physicians’ compliance with treatment guidelines. We hypothesise that teleconsulting support will improve patient outcomes.

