### 3.2. Outcomes

The primary outcome will be a composite of all-cause mortality or one or more hospital readmissions. Any pre-hospital or hospital stay because of heart failure will be considered as a readmission [42,43]. Secondary outcomes will include hospital-free days within 180 days [44,45,46], serious adverse events (defined as any adverse event that results in death, is life-threatening, requires hospitalisation or prolongation of existing hospitalisation, or results in persistent or significant disability or incapacity, measured in municipality admission reports), frequency and intensity of heart failure signs and symptoms, measured using the Symptom Status Questionnaire—Heart Failure—Brazilian Version (Appendix A) [40,41], computed as a 0 to 84 score, and health-related quality of life, measured using the EQ-5D-5L questionnaire [37,38] scored using a value set validated for the Portuguese version [39] on a visual-analogic scale (0 to 100).

An exploratory outcome will be physicians’ adherence to guidelines, comparing prescription data to guidelines and quality standards using a compliance score (Table A1 in Appendix B) [47,48,49,50]. We will measure all outcomes at the patient level, at baseline when meaningful, and after six months of allocation.

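### The sample size uses an annual composite rate (40.1% per year), unconverted, as the control risk for a six-month primary outcome, so the stated 80% power is wrong as written

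*Protocol article*

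**What the plan says.** **Time horizon of the outcome.** The Abstract states: "The primary outcome will be a composite of mortality and hospital admissions after six months". Section 3.2 agrees: "We will measure all outcomes at the patient level, at baseline when meaningful, and after six months of allocation". Table 1 places the readmission and mortality assessment at the six-month close-out.

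**Inputs to the sample size (section 2.11.1).** The control figure comes from a European heart failure survey, "which reports a composite index of readmissions and mortality of 40.1% per year [19". The effect follows: "The estimated effect size based on similar interventions described in the literature is 30% [27". For clustering: "Assuming an intra-cluster correlation (ICC) of 0.05 based on similar studies in primary care [28". The result is "a minimum of 72 clusters of 10 patients in each cluster are necessary to detect a 15% difference in the primary outcome". The error rates attached to this result are 5% for type I and 20% for type II, hence the 80% power.

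**Planned enrolment.** The Abstract rounds this up: "We will include 10 patients per each of the 80 enrolled practices (n = 800".

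**Use of the power figure.** Section 2.11.2 rests the main conclusions on the primary outcome at p < 0.05 and repeats the 80% power. It also judges whether statistical and clinical significance thresholds are met by reference to the effects and power estimates behind the sample size. Section 2.11.1 adds that power for the remaining outcomes was estimated from the same sample size.

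**The concern.** A proportion accrued over one year is not the proportion expected at six months. Unless almost all of the year's events fall in the first half, the six-month control risk is below 40.1%. For a fixed relative reduction, a lower control risk means a smaller absolute difference and less power.

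Two effect sizes also stand side by side, 30% and 15%, without saying whether either is relative or absolute. The 80% power is attached to the 15%.

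What is at stake is interpretation. The protocol makes its power estimate part of how the result will be judged, and section 2.8 has conclusions written before unblinding and not revised afterwards. If the stated power is too high, a non-significant result may be taken as stronger evidence against teleconsultation support than the trial can give.

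**Working it through.** **Inputs.** From section 2.11.1: control figure 40.1% per year, effect 30%, ICC 0.05, 10 patients per cluster, type I error 5%, power 80%. From section 2.1: 1:1 allocation. The 5% is taken as two-sided, which the protocol does not state.

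**Step 1: reproduce the plan's figure.**
- Design effect = 1 + (10 − 1) × 0.05 = 1.45.
- The 30% read as relative: 0.401 × 0.70 = 0.2807, a difference of 12.03 points.
- Two-proportion formula with pooled variance, two-sided 5%, 80% power: 242.5 per arm before clustering.
- 242.5 × 1.45 = 351.6 per arm, so 36 clusters of 10 per arm and **72 in total**, an exact match. Power at 720 patients is then 80.9%, and at 800 it is 84.8%.
- Variants for the same effect: unpooled variance gives 70; unpooled plus one cluster per arm, 72; continuity correction, 76; one-sided, 56.

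**Step 2: try the printed 15%.**
- 15 absolute points (40.1% vs 25.1%): 46 clusters, or 50 with continuity correction. No control risk from 20% to 60%, in one-point steps, gives 72.
- 15% relative (40.1% vs 34.1%): 294 clusters.

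Of the effects the section cites, only the 30% read as relative gives 72 clusters, and it does so with the annual figure unchanged.

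**Step 3: move the control risk to six months.** The protocol gives no six-month risk, so the values below are assumptions. Under a constant hazard, 1 − (1 − 0.401)^0.5 = 0.226. Halving gives 0.2005. Higher values represent risk concentrated soon after discharge. Effective patients per arm are 360/1.45 = 248.3 (720 patients) and 400/1.45 = 275.9 (800 patients).

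Power for a 30% relative reduction, ICC 0.05:

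| Six-month control risk | Intervention risk | 720 patients | 800 patients | Clusters of 10 for 80% power |
|---|---|---|---|---|
| 20.05% (half the annual figure) | 14.0% | 43% | 47% | 178 |
| 22.6% (constant hazard) | 15.8% | 48% | 52.5% | 154 |
| 25% | 17.5% | 53% | 58% | 136 |
| 30% | 21.0% | 63% | 68% | 108 |
| 35% | 24.5% | 73% | 77% | about 88 |
| 40.1% (as in the plan) | 28.1% | 81% | 85% | 72 |

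With 800 patients, power reaches 80% at a control risk of about 37%. With 720 patients it does so at about 39.5%.

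**Step 4: smallest relative reduction detectable with 80% power at 800 patients.** About 43% at a control risk of 20%, 40–41% at 22.6%, 34% at 30% and 31% at 35%.

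**The case against.** **Early risk after discharge.** This is the strongest objection. Section 2.3.1 enrols patients discharged within the past month, section 3.2 counts pre-hospital as well as hospital stays for heart failure, and 51% of the feasibility cases were in NYHA class III or IV. All of this suggests a six-month risk above the constant-hazard 22.6%. The point stands as far as it goes: 22.6% is one scenario and not a best estimate. But the protocol does not offer this as its reason for using 40.1%. Even at 35%, power with 800 patients is 77%.

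**Ample power for the stated 15%.** The protocol ties its 80% to a 15% difference and not explicitly to the 30% effect. If 15 absolute points were meant, power would exceed 99% at a 22.6% control risk with 720 patients. But that would be a 66% relative reduction (15/22.6), more than twice the cited effect, and it does not give 72 clusters. The relative 30% remains an inference from back-calculation, though the only reading of the cited effects that fits. What stands is that the two figures must be reconciled.

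**Imprecision will be visible.** Section 2.11.2 promises a relative risk with a 95% confidence interval, which limits the harm from a misstated power. It does not remove it, because the same section also uses the power estimates in interpretation.

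**A stronger reading to avoid.** A reader might infer that the trial's true power is known to be about one half, or that it must recruit many more practices. The documents support neither. They give no six-month risk, and near-even odds arise only in the lower part of the assumed range.

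**Conclusion.** Wrong as written. An annual figure was used without conversion as the control risk for a six-month outcome, and the plan's own 72 clusters show it. The 15% difference printed with the 80% power does not match those 72 clusters on either scale.

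The size of the shortfall is conditional. For a 30% relative reduction with 800 patients, power runs from about 47% to 77% over assumed six-month risks of 20% to 35%. With 720 patients the range is about 43% to 73%. These figures assume an ICC of 0.05 at every control risk, equal clusters of 10, a two-sided 5% test and no loss to follow-up; losses would lower them. If the 30% were a hazard reduction, power under a constant hazard would be lower too, at about 41% (720) and 45% (800).

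**What to change.** In section 2.11.1:
- Replace the annual figure with a six-month control risk, give its source or basis, and show a range, for example 20–35%.
- Say whether the target effect is relative or absolute, and reconcile the 30% and 15% figures so that the stated number of clusters follows from the stated effect.
- Report, over that range, the power that 80 clusters of 10 give for the target effect and the smallest effect detectable with 80% power (about a 40–41% relative reduction at 22.6%).

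In section 2.11.2, replace the 80% power statement and the power-based interpretation step with the restated figures. Power quoted for the remaining outcomes should be checked for the same time-scale problem.

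This is a wording change, best made before the blinded conclusions of section 2.8 are drafted. It needs no change in enrolment or follow-up. The only cost is a less favourable stated power.

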#### 2.11.2. General Analysis

We will conduct all analyses according to the intention-to-treat principle, where we analyse data as randomised regardless of adherence to the research protocol. An additional per-protocol analysis will be performed for exploratory reasons if the drop-out rate exceeds 5% of the total trial population. We will assess whether the statistical and clinical significance thresholds apply [30], based on the estimated intervention effects and power estimations used in the sample size.

We will base our main conclusions on the primary outcome, following the intention-to-treat principle, assuming a type 1 error threshold of 5% (*p* < 0.05), with the relative risk and confidence intervals (CIs) calculated at the 95% level and a type 2 error threshold of 0.2 (80% statistical power).

Regression analyses will be adjusted for the factors used in the randomisation (the exclusive presence of the family health strategy model in the practice and the social development index stratum), assessing for significant interactions between them and the outcome variables. We will consider the results of secondary or exploratory outcomes as hypothesis-generating only. No subgroup analysis besides the one using the stratification factors is planned; if executed, these results will also be hypothesis-generating only.

Categorical variables will be described as absolute and relative frequencies, and continuous variables as medians (interquartile range) or means (standard deviation) according to the distribution of the variable. Missing data will be handled according to Jakobsen’s recommendations [31]; briefly, we will include participants in the primary analysis of all outcomes and anticipate a less than 5% missing value rate. We will then perform a secondary analysis considering the use of multiple imputations and present best-worst and worst-best case scenarios if it is not valid to ignore missing data.

To account for clustering within each primary care practice, all outcomes will be analysed using generalised estimating equation methods (GEE) [32]. All analyses will additionally be adjusted for the stratification variables used in the randomisation. The software R (R Foundation for Statistical Computing, Vienna, Austria; version x64 3.6.0, including the package “geepack” for GEE) [33] and STATA will be used for statistical analysis.

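### The 15% difference given as the detectable effect does not follow from the sample-size inputs; the 72 clusters match a 30% relative reduction, so the count stands and the reported effect is wrong

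*Protocol article*

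**What the plan says.** Section 2.11.1 (Sample Size) takes its control risk from a European survey that "reports a composite index of readmissions and mortality of 40.1% per year". It continues: "The estimated effect size based on similar interventions described in the literature is 30"%. It then sets the clustering assumption ("Assuming an intra-cluster correlation (ICC) of 0.05") and concludes that "a minimum of 72 clusters of 10 patients in each cluster are necessary to detect a 15% difference in the primary outcome", with a 5% type I error and 80% power. Neither the 30% nor the 15% is labelled as relative or absolute, and nothing connects the two.

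Section 2.11.2 (General Analysis) will assess whether thresholds for statistical and clinical significance apply, "based on the estimated intervention effects and power estimations used in the sample size". The same section names the relative risk as the effect measure. The Abstract and section 2.6 plan 80 practices with 10 patients each, 800 in all.

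**The concern.** Two effect sizes stand in one paragraph, and only one of them can have produced the 72. They are not the same effect on two scales: 30% of 40.1% is 12.0 points, and 15 points out of 40.1% is a 37.4% relative reduction.

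The figure is used again. Because section 2.11.2 ties its significance assessment to the sample-size effect, a reader working on the relative-risk scale could take the reference value as 0.70 (30% relative), 0.85 (15% relative) or 25.1/40.1 = 0.63 (15 points). An observed relative risk of 0.80 would reach the second and miss the other two. A reader who takes 15% as relative would also believe that the trial has 80% power for an effect for which it has about 30%.

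**Working it through.** **Inputs from section 2.11.1:** control risk p1 = 0.401, ICC = 0.05, m = 10 patients per cluster, power 80%, type I error 5%. Allocation is 1:1 (section 2.1).

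**Assumption:** a two-sided test, so z = 1.960 and 0.842. The article does not state the sidedness. The 40.1% is used as the article uses it; whether a yearly rate suits a six-month outcome is a separate question and does not enter here.

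**Formulas**
- Design effect: 1 + (m − 1) × ICC = 1 + 9 × 0.05 = 1.45.
- Patients per arm before clustering (pooled): n = [1.960 × √(2p̄(1 − p̄)) + 0.842 × √(p1(1 − p1) + p2(1 − p2))]² / (p1 − p2)², where p̄ is the mean of p1 and p2.
- Patients per arm before clustering (unpooled): n = (1.960 + 0.842)² × [p1(1 − p1) + p2(1 − p2)] / (p1 − p2)².
- Clusters per arm: n × 1.45 / 10, rounded up; doubled for the total.

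**Step 1: reproduce the 72.** Read the 30% as relative: p2 = 0.401 × 0.70 = 0.2807.
- Pooled: n = [1.960 × √0.4493 + 0.842 × √0.4421]² / 0.01447 = 242.5. Then 242.5 × 1.45 / 10 = 35.2, so 36 per arm and **72 in total**.
- Unpooled: n = 239.8, giving 34.8, so 35 per arm and 70 in total.
- An iterated t-based cluster formula gives 72; a continuity correction gives 76.

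**Step 2: try the 15%, and compare power.**

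| Effect from 40.1% | Intervention risk | n per arm before clustering (unpooled/pooled) | Total clusters needed (unpooled/pooled) | Power, 72 clusters | Power, 80 clusters |
|---|---|---|---|---|---|
| 30% relative (12.0 points) | 28.1% | 239.8 / 242.5 | 70 / 72 | 81% | 85% |
| 15 points | 25.1% | 149.4 / 152.1 | 44 / 46 | 95% | 97% |
| 15% relative | 34.1% | 1008.5 / 1011.2 | 294 / 294 | 28% | 31% |

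The power columns use the pooled formula with 36 or 40 clusters per arm, that is, 360/1.45 = 248.3 or 400/1.45 = 275.9 effective patients per arm.

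**Step 3: look for another reading that rescues the 15%.**
- *Another control risk.* With two-sided testing, a 15-point difference needs most patients when the risks straddle 50% (57.5% and 42.5%). That gives n = 173.2 and 173.2 × 1.45 / 10 = 25.1, so 26 per arm and 52 in total. At this ICC and cluster size no control risk brings 15 points up to 72.
- *A one-sided test.* The pooled counts fall to 36 for 15 points and 232 for 15% relative. Neither is 72. The 30% relative effect would then need 56.
- *72 clusters per arm.* The plan has 80 in total, and 144 clusters would detect 8.5 points.
- *30% as an absolute difference.* This needs about 10 clusters.

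**Step 4: the difference actually detectable from 40.1% at 80% power.** It is 11.9 points (29.7% relative) with 72 clusters and 11.3 points (28.2% relative) with 80.

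**The case against.** The strongest reply is that nothing in the design depends on the wrong figure. The 72 follows from two numbers printed in the same section, the trial enrols 80 clusters, and power for the 30% relative effect is about 85%. That stands.

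A reader might infer from the 28% to 31% figures that the trial is underpowered. The article does not support this: those figures apply only if a 15% relative reduction was the true target, and the match to 72 points elsewhere.

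A reader might also infer that the success criterion can be chosen once results are known. That goes too far. Section 2.11.2 fixes the main conclusion separately: the primary outcome, intention to treat, p < 0.05, and a relative risk with a 95% interval. Section 2.8 provides for blinded statisticians, groups coded A and B, and abstracts drafted before unblinding whose conclusions will not be revised. How the sample-size effect enters the clinical-significance step depends on a cited source that is not at hand. What remains is an ambiguous reference value for that additional assessment.

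Finally, the article does not say that the 30% is relative or that the test is two-sided. The first is inferred from the exact match to 72 (70 or 76 under other formulas). The second is an assumption. Neither caveat rescues the 15%, which fails under every variant tried.

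**Conclusion.** The detectable difference in section 2.11.1 is misstated. On the section's own inputs, 72 clusters of 10 correspond to a 30% relative reduction (12.0 points). They are well above the 44 to 46 needed for 15 points and about a quarter of the 294 needed for 15% relative. The cluster count and the planned enrolment are not in error. The point is more than clerical only because section 2.11.2 refers its significance assessment back to this effect. The verdict rests on two-sided testing and on 40.1% as the control risk. That the 30% relative effect was the one used is a strong inference, which the sponsor should confirm.

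**What to change.** The sponsor should first confirm that the 30% is a relative reduction. Then:

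1. In section 2.11.1, replace the 15% figure with a 30% relative reduction (40.1% to 28.1%, 12.0 percentage points).
2. In section 2.11.2, state that this single effect, on the relative-risk scale of the analysis, is the sample-size effect to which the significance assessment refers.

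If 15% was really intended, keep it, give its scale, and restate the power with 72 to 80 clusters: about 95% to 97% for 15 points, or 28% to 31% for 15% relative.

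The cost is one corrected sentence and one clarifying sentence, made before outcome data are seen. Enrolment does not change.
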